## Abstract

**Introduction:**

Post-Acute Sequelae of SARS-CoV-2 Infection (PASC) presents a multifaceted interplay of demographic, clinical, environmental, and socioeconomic factors. Quantification at the individual level of these factors remains underexplored. Our study aims to address this knowledge gap by analyzing the long-term health implications of PASC, utilizing a comprehensive integration of spatiotemporal, clinical, environmental, and socioeconomic data.

**Methods and analysis:**

The study will enroll over 4,000 confirmed COVID-19 patients from Gansu Provincial Hospital, treated from December 2022 to May 2023, as the baseline. These patients are spread across 14 cities in Gansu Province, with geographic coordinates ranging from 92°13′E to 108°46′E and 32°31’N to 42°57’N. Follow-ups will be conducted via structured telephone interviews at 24, 36, and 48 months post-discharge, from 2024 to 2027, to assess PASC and long-term health outcomes. Participants will be categorized into three age groups: children and teenagers (birth to 18 years), adults (18–65 years), and the older adult (over 65 years). Environmental and socioeconomic data corresponding to each case are also integrated. The primary objective is to assess the persistence and long-term health outcomes of PASC symptoms. Secondary objectives focus on evaluating the acute infection phase, its progression, and the efficacy of medical management strategies in influencing PASC trajectories. Mixed-effects models will be utilized to evaluate the impact of various factors on PASC, while spatiotemporal analyses will explore the correlations between environmental and socioeconomic conditions and the diagnosis and recovery trajectories of PASC.

**Ethics and dissemination:**

The Gansu Provincial Hospital’s research ethics committee has approved this study protocol. Participation will be voluntary, with informed consent obtained from all participants. Study results will be published in peer-reviewed journals.

**Clinical trial registration:**

ChiCTR2400091805.

## Introduction

Post-Acute Sequelae of SARS-CoV-2 Infection (PASC), commonly referred to as Long COVID, encompasses a broad spectrum of persistent symptoms and medical complications that continue well beyond the initial COVID-19 infection phase (1–6). Symptoms varies widely, ranging from mild, non-specific issues like fatigue and headaches to severe, debilitating conditions including cardiopulmonary abnormalities and significant neurological deficits (7, 8). These manifestations significantly impair quality of life and pose ongoing challenges to global healthcare systems (9).

The risk factors contributing to PASC are not well understood. A complex array of demographic, clinical, environmental, and socioeconomic elements, may influence PASC (10, 11). There is substantial evidence suggesting that the interplay between biological and environmental components, including air quality, temperature, humidity, and pollution levels, significantly impacts respiratory illnesses, including COVID-19 (12–16). These conditions exacerbate respiratory symptoms and increase the risk of severe complications (14, 15). Socioeconomic disparities also play a crucial role, influencing individuals’ vulnerability and resilience to COVID-19 and its prolonged effects (17). Factors such as income inequality, access to healthcare, housing quality, and employment status profoundly affect an individual’s risk of virus exposure and their ability to receive timely and adequate medical care (18). Education level, social support networks, and community resources are pivotal in determining an individual’s capacity to manage and recover from the infection (19).

Despite established correlations between these variables and outcomes in respiratory and viral diseases, the specific impacts of environmental and socioeconomic conditions on the severity and manifestation of PASC remain insufficiently explored (20–22). Furthermore, the interactions between individual characteristics and environmental risks introduce complex pathways through which PASC develops and progresses (23). For example, residents of socioeconomically disadvantaged areas may encounter increased exposure to environmental hazards and have restricted access to healthcare services, thereby intensifying their risk of developing severe PASC symptoms. Nevertheless, there is a significant gap in comprehensively quantifying these risk factors at the level of individual patients, especially in identifying the interactions between personal characteristics and environmental risks. This deficiency underscores the necessity for an integrated approach that accounts for both individual and environmental risks in the personalized management of PASC patients. Developing a better understanding of these interactions is essential for formulating holistic strategies to prevent and mitigate the long-term health effects of COVID-19 across diverse populations. Such strategies will necessitate enhancing the precision and efficacy of interventions tailored to meet the unique needs of individual patients.

Given the complexities inherent in PASC, our research adopts a comprehensive and methodical approach to elucidate how environmental and socioeconomic variables influence the progression and recovery patterns of PASC across diverse demographic segments. This longitudinal study encompasses over 4,000 hospitalized COVID-19 patients from 14 cities across Gansu Province (425,800 square kilometers) (24), leveraging its unique geographic and climatic diversity (Figure 1). Positioned at the intersection of China’s Qinghai-Tibet, Loess, and Inner Mongolia plateaus, Gansu spans a wide range of landscapes, from mountainous terrains to vast plateaus, with elevations ranging from approximately 600 to over 5,600 meters and mean annual temperatures varying between −8 and 14°C (24–26). These environmental conditions are coupled with significant disparities in air pollution levels, as median annual concentrations of fine particulate matter (PM2.5) range from approximately 12–41 μg/m^3^, while sulfur dioxide (SO_2_) concentrations vary from 7 to 40 μg/m^3^ (27, 28). Such fluctuations in air quality, combined with varying levels of urbanization and green space coverage—quantified by the normalized difference vegetation index (NDVI), which ranges from nearly 0 to 1 (29), are likely to influence respiratory health and long-term COVID-19 outcomes. Economic and healthcare disparities further compound these environmental differences, as per capita gross domestic product (GDP) across the region varies nearly tenfold, from approximately 20,000 to over 150,000 Chinese yuan (30). Access to healthcare resources also differs significantly, with some cities having nearly twice the number of hospital beds per thousand people compared to others (30). This broad spectrum of environmental, economic, and healthcare conditions provides an ideal framework for investigating how these factors collectively shape the long-term impacts of COVID-19, particularly in relation to PASC risk and recovery trajectories. By systematically integrating these variables, our study aims to develop a more comprehensive understanding of PASC and inform targeted interventions that address both individual and population-level health disparities.

**Figure 1 fig1:**
[figure not shown]
Geographic distribution of environmental and socioeconomic factors across 14 cities in Gansu Province, 2022. This figure illustrates key environmental and socioeconomic indicators across the study region, including: **(A)** Elevation, **(B)** Annual Mean Temperature, **(C)** PM2.5 Concentration, **(D)** Sulfur Dioxide (SO₂) Levels, **(E)** Normalized Difference Vegetation Index (NDVI), **(F)** Gross Domestic Product (GDP) per Capita, **(G)** Median Income of Urban Residents Receiving Minimum Living Allowance, **(H)** Number of Hospital and Health Center Beds per 1,000 People, and **(I)** Paved Road Area per Capita.

The diverse environmental and socioeconomic conditions across the study region provide a unique framework for investigating how these factors interact with age-related biological differences to shape the progression and recovery of PASC. This study employs a longitudinal design to systematically track COVID-19 patients over time, allowing for an in-depth analysis of how environmental exposures, economic disparities, and individual characteristics influence PASC risk and long-term outcomes. By integrating spatiotemporal data with patient health records, we aim to capture the dynamic nature of disease progression across different demographic groups. Furthermore, examining the interplay between environmental pollutants, healthcare accessibility, and socioeconomic determinants will offer a more comprehensive understanding of the broader public health implications of PASC. Through this multidisciplinary approach, our study seeks to inform the development of targeted interventions and personalized treatment strategies, ultimately contributing to improved patient care and more effective public health policies.

## Methods and analysis

### Study population

This prospective cohort study, will enroll over 4000 individuals with RT-PCR-confirmedSARS-CoV-2 at baseline, hospitalized at Gansu Provincial Hospital in China from December 2022 to May 2023 (Gansu PASC dataset). Aligning with methodologies from other PASC research, we will gather comprehensive health data during the patients’ initial hospitalization due to COVID-19 (31). The data collection will include extensive hospital records from their acute COVID-19 admissions, capturing demographic information, clinical data, comorbidities, pre-existing symptoms, and other relevant health details.

The patients were from all 14 cities in Gansu Province (92°13′E-108°46′E, 32°31’N-42°57’N), with various environmental and socioeconomic backgrounds. The municipal geographic coordinates of the 14 cities are detailed as follows: Lanzhou (103°51′E, 36°3’N); Jiayuguan (98°23′E, 39°80’N); Jinchang (102°19′E, 38°52’N); Baiyin (104°14′E, 36°55’N); Tianshui (105°72′E, 34°58’N); Wuwei (102°64′E, 37°93’N); Zhangye (100°45′E, 38°92’N); Pingliang (106°66′E, 35°54’N); Jiuquan (98°49′E, 39°73’N); Qingyang (107°64′E, 35°71’N); Dingxi (104°59′E, 35°61’N); Longnan (104°96′E, 33°37’N); Linxia Hui Autonomous Prefecture (103°21′E, 35°60’N) and Gannan Zang Autonomous Prefecture (102°91′E, 34°98’N). Baseline data will be collected using hospital records, and follow-up assessments will be performed at 24-, 36-, and 48-months post-discharge via structured telephone interviews (Table 1). Exclusion criteria are limited to individuals without available contact details, those who deceased during hospitalization or follow-up, those who declined to participate, and those unreachable for follow-up assessments.

**Table 1 tab1:** Evaluation parameters at baseline and follow-up visits.

Evaluation parameter	Baseline°	Follow-Up°° (telephone interviews)		
	(Hospital admission)	Visit 1 (24 m)	Visit 2 (36 m)	Visit 3 (48 m)
Informed consent	x			
Inclusion criteria met	x			
Demographics*	x			
Environmental/socio-economic factors†	x			
Symptoms‡	x	x	x	x
Life styles¶	x	x	x	x
Vaccination information**	x			
Reinfection††		x	x	x
Recovery condition‡‡		x	x	x
Comorbidities¶¶	x			
Laboratory test results***	x			
Treatment†††	x			
Clinical outcomes	x			
Medical management‡‡‡		x	x	x
Assessment Tools¶¶¶				
EQ-5D-5L score (Adults)	x	x	x	x
mMRC score (Adults)	x	x	x	x
GAD-7 score (Adults)	x	x	x	x
PHQ-9 score (Adults)	x	x	x	x
FSS score (Adults)	x	x	x	x
ISI score (Adults)	x	x	x	x
EQ-5D-Y (Children 4–15 years)	x	x	x	x
PROMIS (Children 8–17 years)	x	x	x	x
SDQ score (Children 4–17 years)	x	x	x	x

°Baseline Assessment: Conducted at the time of hospitalization for COVID-19 at Gansu Provincial Hospital from 2022 to 2023.

°°Follow-Up Visits: Conducted via structured telephone interviews at three time points from 2024 to 2027.

Visit 1 (24 months post-discharge): PASC diagnosis.

Visit 2 (36 months post-discharge): Long-term outcome assessment.

Visit 3 (48 months post-discharge): Final long-term outcome assessment.

*Demographics: Includes age, gender, ethnicity, marital status (for adults), residential status during infection, education background, personal finances (for adults), work status (for adults), and BMI. These details are tailored to ensure age-appropriateness, with specific personal and professional information omitted for children.

†Environmental/socio-economic Factors: Encompasses sulfur dioxide (SO_2_), nitrogen dioxide (NO_2_), ozone (O_3_), particulate matter 10 (PM_10_), particulate matter 2.5 (PM_2.5_), Normalized Difference Vegetation Index (NDVI), temperature, precipitation, relative humidity, wind speed, per capita GDP, income levels, employment status, job types, education level, and living condition. This comprehensive data helps examine the environmental contexts affecting health outcomes.

‡Symptoms Monitoring: Tracks a wide array of symptoms across various systems.

Respiratory: Difficulty breathing, cough, chest pains.

Digestive: Abdominal pain, diarrhea, nausea, vomiting, loss of appetite, constipation.

Cardiovascular: Palpitations, tachycardia, bleeding.

Musculoskeletal: Arthralgia, myalgia, impaired functioning and mobility.

Nervous System: Headaches, dizziness, “brain fog,” sensory impairments, insomnia, and other sleep difficulties.

Other: Fever, fatigue, skin rashes, irregular menstrual cycles (in females over 12 years of age), erectile dysfunction (in males).

¶Lifestyle Factors: Includes smoking and drinking status, providing insights into behaviors that may influence disease progression and recovery.

**Vaccination Information: Documents the dose and timing of COVID-19 vaccinations, critical for assessing vaccine efficacy and patient immunity.

††Reinfection Data: Tracks instances of SARS-CoV-2 reinfection, including timing and test results (PCR, antigen, self-reported symptoms), to understand immunity and disease dynamics.

‡‡Recovery Assessment: Includes a single question about recovery perception post-COVID-19, with responses categorized as yes, no, or unsure.

¶¶Comorbidities: Comprehensive data collection on conditions such as hypertension, various cardiovascular and respiratory diseases, diabetes, chronic liver and kidney diseases, metabolic disorders, nervous system diseases, psychiatric conditions, cancers, rheumatism, tuberculosis, and anemia, essential for assessing co-impact on health outcomes.

***Laboratory Test Results: Analysis of blood count, electrolytes, renal and liver functions, inflammatory markers, and coagulation profiles to provide a physiological snapshot of health impacts.

†††Treatment: Detailed record of all treatments administered, including medications, oxygen therapy, mechanical ventilation, ICU care, and other interventions, helping to correlate treatment strategies with outcomes.

‡‡‡Medical management: Information of visiting a doctor for any reason and treatment undertaken during follow-up.

¶¶¶Assessment Tools: Includes the 5-level EQ-5D version (EQ-5D-5L), The Modified Medical Research Council (mMRC) Dyspnea Scale, The Generalized Anxiety Disorder-7 (GAD-7), the Patient Health Questionnaire-9 (PHQ-9), The Fatigue Severity Scale (FSS), The Insomnia Severity Index (ISI), The EuroQol Five-Dimension Youth Questionnaire (EQ-5D-Y) assesses health-related quality of life, The Strengths and Difficulties Questionnaire (SDQ), The Patient-Reported Outcomes Measurement Information System (PROMIS).

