### Outcomes

#### Primary outcome

The primary objective of this study is to assess the persistence and long-term health outcomes of PASC symptoms. The diagnosis of PASC will be formally established during the first follow-up visit to ensure accurate identification and differentiation from pre-existing conditions, while long-term health outcomes will be evaluated at the second and third follow-up visits (Table 1). Our diagnostic protocol follows the criteria outlined in the WHO definition (32), and utilizes structured telephone interviews for initial PASC assessments (33, 34). PASC symptoms typically emerge at least 3 months after the initial SARS-CoV-2 infection and persist for a minimum of 2 months. To ensure an accurate diagnosis, symptoms must not have been present in the 180 days before infection (35). The initial follow-up visit, conducted 12 months post-diagnosis, confirms the presence and persistence of PASC symptoms, which are systematically evaluated across multiple organ systems, including respiratory, digestive, cardiovascular, musculoskeletal, and neurological functions, as well as general symptoms such as fatigue and fever. Symptom severity is quantitatively assessed using a four-point Likert scale to provide a structured and standardized evaluation of PASC’s impact on patient well-being (36, 37). To further validate symptom emergence and progression, our follow-up protocol differentiates post-COVID-19 manifestations from pre-existing conditions. Aligned with established research protocols, our multidisciplinary (MDR) team conducts follow-ups to collect comprehensive data on new diagnoses and medical consultations, allowing for the identification of secondary conditions potentially associated with PASC (38).

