#### Follow-up assessments

We will conduct telephone follow-ups to diagnose PASC, employing methodologies consistent with those used in major global studies (43, 44). This approach is designed to enhance patient engagement and follow-up compliance, ensuring the inclusion of a broad demographic across diverse geographic locations. Follow-up visits will take place at three time points between 2024 and 2027: Visit 1 (24 months post-discharge) for PASC diagnosis, Visit 2 (36 months post-discharge) primarily for long-term outcome assessment, and Visit 3 (48 months post-discharge) for the final long-term outcome evaluation. During these follow-ups, we will assess the persistence of symptoms and track overall health status, alongside collecting updated information on demographics, environmental exposures, residential status post-infection, lifestyle changes, vaccination history, and hospitalization duration. The monitoring process will also include tracking reinfection cases, post-discharge mortality, the emergence of new symptoms, and changes in health status compared to the initial COVID-19 onset. Consistent with methodologies applied in similar studies (45, 46), our research incorporates patient consultations and provides recommendations for further medical evaluation based on symptoms reported during telephone interviews. However, direct medical interventions are not conducted as part of this study.

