Despite the strengths of our study, we acknowledge several limitations and have devised strategies to address them effectively. Firstly, our study is based in Gansu Province, China, involving data from 14 cities, each with unique environmental and socioeconomic characteristics. While this provides a rich dataset within a specific geographic region, it limits broader geographic representation. To address this, we have included multiple sites chosen for their environmental diversity, particularly focusing on urban settings across different regions. This strategic selection helps control environmental factors that could influence health outcomes related to PASC. Secondly, our current study setup does not include direct comparisons with other cities or countries, which restricts our ability to generalize findings across different global environments. We plan to expand our analysis to include such comparisons as comparable data becomes available, allowing for a more comprehensive evaluation of environmental and socioeconomic impacts on PASC rates and health outcomes. Thirdly, the non-random nature of our patient recruitment might introduce selection bias, and the reliance on telephone questionnaires could lead to recall bias, particularly as participants may not accurately remember past symptoms. To mitigate these issues, we use advanced statistical methods to control for potential confounders and perform sensitivity analyses to assess the impact of data attrition. Fourthly, an oversight committee is actively involved in monitoring and evaluating the study’s processes to address any unforeseen issues that arise, thereby ensuring the integrity and validity of our research. Plans for further validation through clinical assessments are in place to enhance the reliability of our findings, particularly to address challenges associated with self-reported data. By implementing these strategies, we aim to refine our understanding of PASC and its diverse impacts across different populations, ensuring that our findings are robust and reflective of the true effects of environmental and socioeconomic factors on health outcomes post-COVID-19.

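### The exclusion criteria remove patients who die or become unreachable during follow-up, so cohort membership depends on post-baseline events and PASC estimates are open to bias

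*Protocol article*

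**What the plan says.** The Study population section of the protocol article uses the label "This prospective cohort study" and states that it "will enroll over 4000 individuals with RT-PCR-confirmedSARS-CoV-2 at baseline". It adds that "follow-up assessments will be performed at 24-, 36-, and 48-months post-discharge via structured telephone interviews". The exclusion list that follows is introduced as complete. Besides patients without contact details, it names "those who deceased during hospitalization or follow-up, those who declined to participate, and those unreachable for follow-up assessments".

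Under Primary outcome: "The primary objective of this study is to assess the persistence and long-term health outcomes of PASC symptoms". The same section says: "The diagnosis of PASC will be formally established during the first follow-up visit". Table 1 places that visit at 24 months, with long-term outcomes at 36 and 48 months.

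Three other places bear on the same patients. Follow-up assessments says: "The monitoring process will also include tracking reinfection cases, post-discharge mortality, the emergence of new symptoms". Statistical analysis promises sensitivity analyses under different assumptions about missing data. The limitations part of the Discussion says that the team will "perform sensitivity analyses to assess the impact of data attrition". It also concedes possible selection bias, but attributes it to non-random recruitment and not to these exclusions.

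**The concern.** Membership of a prospective cohort should be settled by what is known at entry. Here two of the listed criteria, death during follow-up and unreachability for follow-up, are known only later, at any time up to 48 months after discharge.

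These events are unlikely to be neutral. The Discussion itself links chronic illness to severe acute disease and prolonged PASC, and air pollution to COVID-19 severity and mortality. On the document's own account, the exposures under study are plausible drivers of both leaving the cohort and having the outcome.

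Three things are at stake. A study of long-term health outcomes would not count the deaths. The attrition analysis would have nobody lost to analyse. And PASC prevalence and risk-factor effects would describe a subset selected after baseline, while being reported as those of the enrolled cohort.

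Excluding in-hospital deaths, refusals and patients without contact details is not part of this point. A post-discharge cohort can set those conditions at entry.

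**Working it through.** **No figure to reproduce.** The article states no PASC rate, mortality, response rate or power, and gives no derivation of the 4,000. The check therefore compares the passages and then uses selection algebra with assumed rates.

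**Passages side by side**

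- *Deaths.* Follow-up assessments tracks post-discharge mortality; Study population makes the same patients ineligible. Both cannot be applied.
- *Losses.* Statistical analysis and Discussion treat lost patients as missing data; Study population puts them outside the cohort. Applied literally, no lost patient remains for the attrition analysis.
- *Partial follow-up.* The exclusion is not tied to a visit. Read literally, a patient interviewed at 24 months who dies or is missed at 48 months becomes ineligible, and the 24-month data go too.

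**Prevalence among those retained** (all rates assumed)

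With true prevalence p and retention r1 (PASC) and r0 (no PASC), observed prevalence = p·r1 / [p·r1 + (1−p)·r0].

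- p = 0.20, r1 = 0.80, r0 = 0.60: 0.16 / (0.16 + 0.48) = 0.25.
- p = 0.30, r1 = 0.60, r0 = 0.80: 0.18 / (0.18 + 0.56) = 0.243.
- p = 0.30, r1 = r0 = 0.80: 0.24 / (0.24 + 0.56) = 0.30, no bias.

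For true prevalence of 20–40% and exclusion differing by 10 to 20 points between those with and without PASC, the shift is about 2 to 7 points in either direction. The sampling 95% half-width at 30% prevalence in 3,200 patients is 1.96·√(0.3·0.7/3,200) = 0.016, or 1.6 points.

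**Odds ratio among those retained** (all rates assumed)

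Observed OR = true OR × (s11·s00)/(s10·s01), where s is retention by exposure (first index) and PASC (second index). Take a true OR of 1.5.

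- Retention depending on PASC only, on exposure only, or on both multiplicatively: factor 1, OR stays 1.50.
- Losses adding up (0.5, 0.7, 0.7, 0.9 for s11, s10, s01, s00): 0.45/0.49 = 0.918, OR 1.38.
- Extra loss only in exposed PASC patients (0.6 against 0.8 elsewhere): 0.48/0.64 = 0.75, OR 1.13.
- Extra loss only in exposed patients without PASC (0.6 against 0.8 elsewhere): 0.64/0.48 = 1.33, OR 2.00.

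**Cost of the literal all-visits reading** (assumed independent 85% at each visit)

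0.85³ = 0.614, so 61% are kept. Of those who complete the 24-month interview, 1 − 0.85² = 0.2775, or 28%, would have that interview discarded for missing a later one.

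**The case against.** The strongest reply is that the sentence is loose drafting. It may simply list who will contribute no follow-up data, and the missingness and attrition analyses make sense only if partly followed patients stay in. No passage says that a completed 24-month interview is thrown away. That is a fair charitable reading, and it may be what is intended. But the list is worded as a closed set of exclusion criteria, and nothing says whether it applies per visit or to the whole study. The text has to be reconciled either way.

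Second, PASC is ascertained only by interview from 24 months. A patient who dies before then has no PASC status under any wording, and rewording recovers no PASC datum. This stands. What can change is whether deaths are reported, whether earlier visits are kept, and whether non-response is modelled. The 25% against 20% illustration is likewise ordinary non-response. The exclusion does not create it, but placing the non-responders outside the cohort removes the basis for showing or correcting it.

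Third, the choice between weighting, competing-event methods and other tools can be left to an analysis plan that is not shown. This is true of the method. It is not true of eligibility, which the article fixes explicitly and an analysis plan would inherit.

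Some stronger readings are tempting and not supported:

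- *That the cohort is defined by PASC itself.* PASC status is not an exclusion criterion.
- *That the estimates are biased, or that survivor selection pulls risk-factor effects toward the null by a known amount.* The document gives no mortality or response rate, and some selection patterns leave the odds ratio untouched. Survivor-bias figures built on shared unmeasured frailty also compare against PASC status in the dead, which no study could observe.
- *That the exclusion shrinks the number interviewed at 24 months, or that 4,000 cannot be the number analysed.* Deaths and non-response reduce interviews equally with or without the rule. The article does not say whether 4,000 is counted before or after exclusions.

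**Conclusion.** The point holds in this form: cohort membership is conditioned on survival and reachability during follow-up, and this contradicts the mortality tracking and the missingness and attrition analyses promised elsewhere in the same article. The contradiction rests on the text alone and needs no assumption.

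The consequence is exposure to bias of unknown size and direction. Prevalence is affected whenever retention is related to PASC. Odds ratios are sturdier and are affected only when retention depends jointly on exposure and PASC in a non-multiplicative way. Under the assumed rates, prevalence moves by about 2 to 7 points and an OR of 1.5 moves to between 1.13 and 2.00; these figures illustrate the mechanism and do not predict this study's results. The 61% applies only if the exclusion is enforced across all three visits and attendance is independent.

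**What to change.** - **Eligibility.** Define it at discharge alive: RT-PCR confirmed, contact details available, and consent given as the ethics approval allows. Delete the follow-up part of the death exclusion and the whole of the unreachability exclusion.
- **Data kept.** State that every completed visit is retained, whatever happens later.
- **Deaths.** Report post-discharge death as an outcome and treat it as a competing or truncating event for PASC.
- **Losses.** Treat unreachable patients as missing data. Weight responders by the inverse probability of response, modelled from the hospital-record baseline. Weighting corrects only for measured factors, so add a sensitivity analysis for unmeasured selection.
- **Reporting.** Say whether the figure of over 4,000 counts eligible or analysed patients, and give the numbers and baseline characteristics of those lost.

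The cost is a change to the eligibility and analysis wording, one response model, and possibly confirmation from the ethics committee that non-responders' records may be used. No new visits are needed.
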